#### Primary and secondary outcomes

The primary outcome is patient-reported coordination of healthcare. Coordination of patient care is a multidimensional concept, often measured in terms of patient reported healthcare received [12]. For this study, a validated patient questionnaire will be applied: the Nijmegen Continuity Questionnaire, a 28-item questionnaire that covers personal coordination of care as well as multi-professional cooperation [13]. The measure has been applied and validated in primary care as well as ambulatory medical specialist care. It has been translated into German, using a forward and backward translation procedure, and pilot tested in a separate sample of patients before the main study began. The 4 items concerning inpatient care will not be used.

The main measures in this study map out the cooperation networks of healthcare providers.

The patient questionnaire will contain questions on healthcare providers involved and their cooperation up to 1 year before measurement. This method was successfully applied in previous research of the principal investigator [11]. The focus of the questionnaire will be on ambulatory cardiac care (primary care physician, physicians’ assistants, cardiologist). Based on previous research of the principal investigator [14], we refrain from measuring networks from the patient relatives’ perspectives.

Additionally, several network characteristics will be calculated from the documented cooperation networks (centrality, density, homogeneity, reciprocity: see section data-analysis), while other network characteristics will be directly measured with questionnaires for providers (opinion leadership, presence of case managers, perceived change of networks). The questionnaire for primary care providers will include questions on the social network and its context: a) presence of opinion leaders for vascular care [14, 15] within and outside of general practices as mentioned by health care providers. Furthermore, b) providers’ self-perception of opinion leadership [15, 16], c) clinical attitudes regarding treatment of vascular patients on which controversy exists, using validated questions with a 5-point Likert scale [14], d) attitudes regarding interprofessional cooperation, using a validated questionnaire [17], e) identification of an appointed case manager for vascular care, if present and f) perceived change in the primary care practice and in the regional network for cardiovascular care (low, moderate, high). We will also include open questions to identify contextual determinants of cooperation between healthcare providers, including factors related to the functioning of primary care teams, financial reimbursement schemes, information technology systems, and health system characteristics.

#### Questionnaires for patients, health care providers and practices

All questionnaires will be sent out after inclusion of the practices and within the first 12 months of the project.

Patients‘questionnaires (see Additional file 4) will include questions on sociodemographic patient characteristics (6 questions), (multimorbid) diseases (2 questions) and disease management programs (2 questions) using standardized questions. Opinions on healthcare providers and healthcare provision by general practitioners and medical specialists in cardiology will be collected through the Nijmegen Continuity Questionnaire described above (24 questions). Additionally, patients will be requested to report on the frequency of contacts with their own GP, cardiologists (6 questions) and other healthcare providers such as physicians’ assistants, other medical specialists, groups for cardiovascular-related sports, pharmacies, podiatries and home care services (1 question). Finally, the patient questionnaire will document aspects of cardiac care delivery, derived from prevailing clinical guidelines (e.g. treatment and counselling received, 10 questions).

Primary care practices will receive a questionnaire on background characteristics of the practice itself (6 questions), staff and education (5 questions), documentation (1 question) and communication with medical specialists (1 question), see Additional file 3.

Primary care providers (physicians, assistants) (see Additional file 2) will complete a questionnaire on sociodemographic data (4 questions), professional career (3 questions), interaction with staff (personalized, 2 questions, similar to a measure used in previous research [10]) and cardiologists (personalized, 2 questions), communication and information exchange with cardiologists (4 questions) as well as information exchange with pharmacists, nutritionists, physiotherapists, elderly care nurses, ambulatory care services, sport groups for rehabilitation patients, sport groups for cardiovascular patients, facilities for rehabilitation, other general practitioners and other practice assistants, psychologists, pneumologists, specialists for internal medicine and medical officers (2 questions, a similar measure was successfully applied in previous research of the principal investigator [10, 14]). Furthermore, they will be asked about their opinion on cardiovascular care and whether they see themselves more as opinion leaders or opinion seekers (16 questions). Finally, they receive questions on team climate within their practice (15 questions). A validated 14-item questionnaire will be used: the Team Climate Inventory, short version [17], and one additional question on factors that could influence health care delivery (1 question).

Physicians’ assistants will receive the same questionnaire and are asked to skip questions explicitly related to physicians.

Cardiologists will be requested to complete a short, written questionnaire (Additional file 1). We will ask sociodemographic and professional characteristics (6 questions) and questions on information exchange with other professionals, such as: general practitioners, pharmacists, nutritionists, physiotherapists, elderly care nurses, ambulatory care services, sport groups for rehabilitation patients, sport groups for cardiovascular patients, facilities for rehabilitation, other practice assistants, psychologists, pneumologists, specialists for internal medicine except cardiology and medical officers (2 questions, see above). Furthermore, they will be asked about their opinion on cardiovascular care (3 questions) and factors influencing health care delivery (1 question).

#### Data-analysis

##### Phase 1. Data-verification

Item response and frequencies of all questionnaire data will be inspected and explored in order to identify selective item-response. Within primary care practices and the local networks of primary care and cardiology practices, the overlap of reported cooperation networks across responders will be examined to get an impression of the reliability and completeness of network data. Reciprocity of reported connections is used as an indicator of reliability of data on presence of connections. If the reciprocity is sufficiently high (> 0.60), missing values will be imputed by available data [18].

##### Phase 2. Construction of cooperation networks

Two networks will be constructed for each of the 40 primary care practices. The first network is provider-reported. Data from primary care providers in a specific practice organisation will be combined in one data-set and links with healthcare providers outside the practice (cardiologists and other providers) are added. The second network is patient-reported. Data from individual patients in a specific practice organisation will be combined in one data-set in order to define the cooperation network from the patient perspective. Identifiers of individuals in the provider- and patient-based networks will be matched in order to examine the overlap between the two types of networks.

##### Phase 3. Descriptive data-analysis (research objective 1)

Data preparation will be done with the statistical package SPSS, while descriptive and comparative analyses will be made using software packages SPSS and R. The measured aspects of coordination and their variation between practices will be displayed descriptively, using suitable summary statistics. The general practices’ networks will be visually displayed in network plots using visualization within R. Descriptive network parameters (size, density, centrality) will be presented, including mean, median, and range of values. Overlap between patient and care provider reported networks will be calculated using correlation/multiplicity measures. Descriptive and visual information will be reported to participating practices as educational feedback.

##### Phase 4. Exploration of network-related determinants of coordination (research objective 2)

Quantitative analysis is primarily focused on the hypotheses concerning network-related mechanisms of coordination, which are specified in the conceptual model.

The respective mechanisms will be examined in two steps:

Step 1: Construction of measures for each practice, calculated from the documented networks or directly from the questionnaires:
opinion leader: presence of a care provider within or outside of a general practice influencing opinions as reported by care providers. (polytomous variable). Additionally, self-perception as an opinion leader by care providers (based on questionnaire).central care provider: degree of the healthcare provider with the highest centrality in the network (count variable, calculated from network data).density of network: proportion of connections of all possible connections (variable with values between 0 and 1, calculated from network data).homogeneity: consistency of clinical attitude views and multiprofessional cooperation (E-I parameter, which has values between − 1 and + 1, calculated from network data).presence of case manager (dichotomous variable, based on questionnaire).network reciprocity: average proportion of network members which can be reached through mutually confirmed pathways (count variable, calculated from network data).perceived change in the network of referral and consultation to other care providers (5-point-likert-scale, based on questionnaire).

Step 2: Analysis of impacts. Potential impact of each of the network characteristics together with patient-reported coordination of care will be examined. The measured and constructed network characteristics will be added to the patient-level data as potential predictors for the patient-reported coordination of care and aspects of cardiac care delivery. We will analyse the provider-reported cooperation networks and the patient-reported cooperation networks separately. Linear or logistic regression models will be applied with distributions and link functions as appropriate for the observed distributions (e.g. normal, binomial, Poisson). Random coefficient models will be used in order to take clustering of data into account (patients with practices). The influence of individual patient characteristics will be explored in further analyses. Although a large number of statistical tests will be applied, we use the conventional *p* < 0.05 as cut-off for significance given the explorative character of the study.

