Coordination of care is influenced by many factors. Firstly, shared ideas about what is desirable practice, such as shared multi-disciplinary clinical guidelines, enhance coordination across different healthcare providers. It is difficult to achieve well-coordinated care, if each healthcare profession and institution follows its own recommendations and these are conflicting with those of others. Secondly, coordination depends on effective cooperation between healthcare providers around individual patients and local populations. This requires adequate information exchange, constructive cooperation behaviours, and good relationships between patients and providers [6]. Cooperation work on a case-by-case basis is time consuming, so much of it takes the format of structured information transfer (e.g. referral letters of general practitioners to other medical specialists). HCPs’ attitudes and competencies influence their interprofessional cooperation. Third, a range of contextual and health system factors (financial, organisational, legal) are barriers or facilitators of well-coordinated care. For instance, if coordination implies additional workload or a financial loss, which is not compensated for, it is unrealistic to achieve improvement in practice.

The proposed study will explore the role of population structure [7], particularly emerging social networks of healthcare providers [8], on healthcare providers’ performance and patients’ experience of healthcare. For this purpose, we will apply social network analysis (SNA) to examine healthcare providers’ cooperation. The usefulness and feasibility of SNA methods were successfully tested in pilot studies [9–11]. The aim of the study is a) to describe and explore variation in information transfer and interprofessional collaboration in ambulatory cardiac care in Germany and b) to describe and explore the role of provider networks from the perspective of patients and providers, focusing on healthcare coordination and the uptake of recommended practices.

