#### Study population and sampling

From publicly available lists of the Statutory Health Insurance Agencies of Baden-Württemberg (KVBW), Rhineland-Palatinate (KVRLP) and Saarland (KV Saarland), primary care practices within designated administrative districts will be randomly drawn and invited to take part in the study until the target sample size has been reached.

To enhance the homogeneity of the study population, we will focus on patients with coronary heart disease (as indicator for atherosclerotic vascular disease) and at least one other chronic disease (chronic heart failure, diabetes mellitus, chronic obstructive pulmonary disease, chronic renal failure or depression). Within these conditions, we will select patients with moderate to high disease severity, using ICD-codes. Primary care practices will be asked to invite 15 patients for the study. Primary care physicians, respectively their assistants, will be asked to generate a list of patients potentially eligible for our study by using their practice’s documentation software. Patients need to have visited the practice within the past 3 months; patients with a short life expectancy or major cognitive limitations will not be approached. The practice generates a printed list and removes potential identifiers except ICD-codes. Afterwards, one member of the research team visits the practice and randomly chooses the desired number of patients from the list. Alternatively, instructions for randomized sample drawing are sent to the practice and staff members choose patients accordingly themselves. The practice is then provided with a sufficient number of blank envelopes and questionnaires through the research team and will send out questionnaires to the selected patients. The patient receives the questionnaire, is free to fill it out and send it back anonymously directly to the research institute. The study was powered to detect a small to medium effect size (*r* = 0.15) on the primary outcome. Power was set at 0.8, significance level at 0.05, and a design effect of 1.4 (40 clusters and an intraclass correlation coefficient of 0.01) was taken into account.

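### Homogeneity of views is measured only by the E-I parameter, which describes whether ties run within opinion groups; a separate measure of agreement in views is needed

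*Protocol article*

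**What the plan says.** The protocol article, Phase 4, Step 1, announces the "Construction of measures for each practice, calculated from the documented networks or directly from the questionnaires". One entry in that list is "homogeneity: consistency of clinical attitude views and multiprofessional cooperation (E-I parameter", with a range from -1 to +1, calculated from network data. The survey section names no other measure of agreement in views.

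Step 2 then states: "The measured and constructed network characteristics will be added to the patient-level data as potential predictors for the patient-reported coordination of care". Patient-reported coordination is the primary outcome.

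The Background gives a reason to expect an effect: "shared ideas about what is desirable practice, such as shared multi-disciplinary clinical guidelines, enhance coordination across different healthcare providers". It adds that coordination is hard to achieve when professions and institutions each follow their own, conflicting recommendations.

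The raw material is described under Primary and secondary outcomes: "clinical attitudes regarding treatment of vascular patients on which controversy exists, using validated questions with a 5-point Likert scale". Density is a separate entry in Step 1: "density of network: proportion of connections of all possible connections".

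**The concern.** The entry names a property of views, their consistency, but the chosen index is a property of ties. E-I compares the number of ties between groups with the number within groups. If providers hold opposing views and mostly deal with their own side, nearly all ties are internal and the index approaches -1. Full consensus gives the same value. The arrangement that the Background describes as harmful can therefore look like the one it describes as helpful.

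The test of the shared-views mechanism is at stake. If E-I is the only measure of homogeneity, an association with coordination, or the lack of one, cannot be attributed to agreement in views. The index combines two things: how opinion is divided, and how strongly ties follow opinion. Reversing its sign does not separate them.

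**Working it through.** **Inputs.** The article gives the index, its range, the unit (one value per practice) and its use as a predictor. It gives neither the formula nor the grouping attribute. I assume the standard formula, with groups defined by attitude. Network sizes and tie patterns below are illustrative assumptions.

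**Formula.** E-I = (E - I)/(E + I), where E is the number of ties between groups and I the number within groups. With all ties internal it is -1, and with all ties external it is +1. This reproduces the stated range.

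**Same value for opposite situations (10 providers, 45 possible ties).**
- Full consensus, all ties present: E = 0, I = 45, E-I = -1.
- Two opposing camps of 5, no cross ties: E = 0, I = 20, E-I = -1.
- Full consensus on that same 20-tie graph: E = 0, I = 20, E-I = -1. Density is 20/45 = 0.44 in both of the last two cases, so adjusting for density cannot tell them apart.
- Five camps of 2, no cross ties: E = 0, I = 5, E-I = -1.

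**Intermediate values.**
- Complete network, split 9:1: E = 9, I = 36, (9 - 36)/45 = -0.60.
- Split 5:5 with 5 cross ties: E = 5, I = 20, (5 - 20)/25 = -0.60.
- Star network whose hub is the only dissenter, so 9 of 10 agree: E = 9, I = 0, E-I = +1.

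**Where the index does work.** In a complete network it follows the split: +0.11 at 5:5, -0.60 at 9:1 and -1 at 10:0.

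**When misranking occurs (8 providers).** Let r be the probability of a cross-group tie divided by that of a within-group tie. A 7:1 team has 21 internal and 7 external pairs; a 4:4 team has 12 and 16. In expected tie counts:
- E-I(7:1) = (7r - 21)/(7r + 21)
- E-I(4:4) = (16r - 12)/(16r + 12)

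| r, same in both teams | 7:1 | 4:4 |
|---|---|---|
| 1/6 | -0.89 | -0.64 |
| 0.25 | -0.85 | -0.50 |
| 1 | -0.50 | +0.14 |

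At any common r above 0 the near-consensus team is closer to -1, which is the right order.

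If r differs between the teams, the ratio E/I is r/3 for 7:1 and 4r/3 for 4:4. The order reverses when r in the divided team is below a quarter of r in the near-consensus team. For example, a 4:4 team with r = 1/6 scores -0.64, whereas a 7:1 team with random mixing (r = 1) scores -0.50.

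**The case against.** A reader might infer that divided practices will be ranked as more homogeneous than near-consensus ones, and that the test is therefore biased. The documents do not support this. The reversal appears only when a homophilous divided team is compared with a near-consensus team whose ties are much less homophilous. The article gives no contact rates by opinion, so neither the frequency nor the size of misranking can be stated.

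A reader might also infer that E-I says nothing about whether providers share views. That goes too far. Among connected providers it shows exactly that, and the exact tie at -1 needs camps with no contact at all.

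The construct can also be defended. The definition joins views with multiprofessional cooperation, and the hypotheses are said to be specified in the conceptual model, a figure not available for this review. If the mechanism there is that cooperating providers are like-minded, E-I is a suitable index, and a spread measure alone would lose the network element. This stands, and it is why E-I should be kept.

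Homogeneity is also one of seven listed measures in an analysis declared explorative. That limits the consequences. Even so, the Discussion says the project will test hypotheses, and the definition still names consistency of views. Density helps only in part, because consensus and division on the same graph share it. If groups were formed by profession instead, E-I would carry no information on views at all. How the attitude answers are grouped is a detail an article may leave to the full plan, and is not part of this point.

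**Conclusion.** The point holds in a limited form. The plan equates consistency of clinical views with an index of homophily of ties and names no other measure of agreement. E-I cannot distinguish consensus from separated camps at its lower extreme, even at equal density. Its intermediate values mix the opinion split with the degree of homophily, as the two networks at -0.60 show. At equal homophily it orders the 7:1 and 4:4 teams correctly, so misranking arises only when homophily differs enough between practices. Its size in this study is unknown.

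The conclusion rests on the standard E-I formula, which fits the stated range, and on groups formed by attitude. The networks are illustrations, not estimates.

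**What to change.** In Phase 4, Step 1, add a separate predictor for agreement in views: the mean absolute pairwise difference (or the SD) of the Likert attitude scores among responding network members, reversed so that a high value means agreement. Where cardiologists are included, use only items common to the primary care and cardiologist questionnaires. Cardiologists receive 3 opinion questions, against 16 for primary care providers on opinion and opinion leadership together.

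Keep E-I, label it as homophily of cooperation ties, and state that it will not be interpreted alone as consensus.

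The cost is one added definition and one more predictor in an exploratory analysis. The attitude items are already planned, so no new data collection is needed. The agreement score has a gap of its own: it covers only providers who answered the attitude items, and the article describes no attitude questionnaire for the other external providers added to the networks.

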#### Data analysis

Data preparation and analyses using the claims data will be performed with the relational database MySQL and R. In the first phase, network characteristics will be calculated wherever possible. These include independent measures that theoretically could influence our outcomes and involve among others: network density and homogeneity, the existence of a central care provider, and change of network composition. As outcomes, we will calculate measures that assess coordination of healthcare: a) the Bice-Boxerman Continuity of Care Index (COC) [25] that indicates the concentration of care with a single provider and b) the Sequential Continuity Index (SECON) [26] that indicates the number of handoffs of information required between providers. Additionally, a more clinically relevant outcome will be included by calculating hospitalization.

In the second phase, we will explore whether the hypothesised network-related mechanisms relating to central care providers, network density, network homogeneity, and change of network composition are associated with measures of coordination of care and hospitalization rates. All analytic analyses will be adjusted for patient characteristics, such as age, sex, and prevalence of comorbidities.

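### The main survey models name only network characteristics as predictors and defer patient characteristics, so case-mix differences between practices can appear as network effects

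*Protocol article*

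**What the plan says.** In the Protocol article, Phase 4 (research objective 2), Step 1 is described as "Construction of measures for each practice, calculated from the documented networks or directly from the questionnaires". Each network predictor is therefore one value per practice, 40 values in all.

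Step 2 is headed as an analysis of impacts and specifies the models: "The measured and constructed network characteristics will be added to the patient-level data as potential predictors for the patient-reported coordination of care". On dependence it says "Random coefficient models will be used in order to take clustering of data into account". No patient covariate is named for these models. The only mention of patient characteristics comes next: "The influence of individual patient characteristics will be explored in further analyses". The same paragraph keeps p < 0.05 as the cut-off and cites the explorative character of the study.

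For the claims data study, the Data analysis section sets a different rule: "All analytic analyses will be adjusted for patient characteristics, such as age, sex, and prevalence of comorbidities".

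The section on questionnaires shows that the patient form covers sociodemographic characteristics (6 questions), diseases (2) and disease management programmes (2).

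**The concern.** This is an observational comparison of 40 practices. If practices whose patients are older or sicker also tend to have denser or more centralised networks, and such patients rate coordination differently, an unadjusted coefficient mixes the two influences.

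The random practice effect gives an appropriate standard error for a practice-level predictor. It leaves the estimate itself exposed to any practice-level difference associated with that predictor.

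The Phase 4 introduction says the quantitative analysis focuses on hypotheses about network mechanisms. The Discussion expects network factors to be used to tailor interventions. A coefficient that partly reflects patient mix would mislead that use. Survey and claims results on shared mechanisms (central provider, density, homogeneity, network change) would also be harder to compare if one set is adjusted and the other is not.

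**Working it through.** **The plan's own figures.** The article gives no figure for confounding, so there is nothing to reproduce on this point. The design inputs used below are 40 practices, 15 invited patients per practice (40 × 15 = 600), an ICC of 0.01 and a planned effect of r = 0.15.

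**Assumed inputs (not in the document).** These are the correlation *a* of a patient case-mix variable with the outcome, the ICC *c* of that variable across practices, and the correlation *ρ* of its practice-level component with the network predictor. Outcome and predictor have unit variance, the network predictor has no true effect, and all 15 patients respond.

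**Spurious slope.** Expected unadjusted slope = a × √c × ρ.

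- A: 0.3 × √0.05 × 0.3 = 0.020, which is 13% of 0.15
- B: 0.3 × √0.10 × 0.5 = 0.047, which is 32% of 0.15
- C: 0.4 × √0.10 × 0.5 = 0.063, which is 42% of 0.15

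**False-positive rate.** Simulation used 4,000 runs per scenario, a residual ICC of 0.01 and a two-sided 5% test at practice level.

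| Scenario | Unadjusted | Adjusted |
|---|---|---|
| No confounding | 0.048 | 0.045 |
| A | 0.079 | 0.049 |
| B | 0.169 | 0.055 |
| C | 0.262 | 0.049 |

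**Analytic check, scenario B.**

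- Between-practice variance not explained by the predictor: 0.09 × 0.10 × (1 − 0.25) + 0.01 = 0.01675.
- Within-practice variance: 0.09 × 0.90 + 0.90 = 0.981; divided by 15, 0.0654.
- Standard error of the slope: √((0.01675 + 0.0654)/39) = 0.046.
- Ratio of slope to standard error: 0.0474/0.0459 = 1.03. With 38 degrees of freedom the rejection probability is about 0.17, in line with the simulation. The same calculation gives about 0.07 for A and 0.26 for C.

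**Consistency with the protocol's ICC.** Case-mix adds a² × c to the between-practice variance: 0.0045 (A), 0.009 (B), 0.016 (C). If the stated 0.01 is the total outcome ICC, A and B fit within it. The same check with total ICC 0.01 then gives about 0.07 and 0.19. C does not fit, so the 26% end needs more practice variation than the plan assumed.

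**Practice and network size.** Density is defined as the "proportion of connections of all possible connections", and the central-provider measure is a raw degree count. With mean degree held at 4, density is 4/(n − 1): 0.57 for 8 members, 0.36 for 12, 0.21 for 20, 0.14 for 30. Size is thus tied to these measures by definition.

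**The case against.** **The article never says that the main models are unadjusted.** This is correct. Exploring the influence of patient characteristics could also mean their own associations or effect modification. But the only predictors named are network characteristics, and patient characteristics are placed in analyses that come afterwards. The concern rests on that stated order as well as on silence.

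**Design already limits case-mix.** Patients must have coronary heart disease plus at least one listed comorbidity, at moderate to high severity, and are drawn at random within practice. This narrows the differences. It still admits five different comorbidities and any mix of age and sex, and random selection within a practice does not balance patients between practices.

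**The claims study is independent.** It has other outcomes and a broader population, so its adjustment rule is not a strict contradiction. It does show that the same project regards age, sex and comorbidity as necessary covariates for overlapping mechanisms.

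**The work is exploratory.** That explains the absence of multiplicity control. It does not reduce bias in a coefficient.

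**A stronger reading is tempting but not supported.** A reader might infer that practice size and location are also left to the later analyses, and that the main models are wrong to omit them. The sentence on later analyses covers individual patient characteristics only. Step 2 does not mention practice size, and a condensed article may leave that to a fuller document. Rural or urban location is not shown to be among the items collected. Adjusting for size is also a real trade-off, since size may be part of the mechanism. If size and density correlated at 0.6 (an assumption), variance inflation would be 1/(1 − 0.36) = 1.56, a standard error about 25% larger.

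**Conclusion.** The concern holds for patient case-mix. As written, the main survey tests of network characteristics are most naturally read as not case-mix adjusted, and the random practice effect does not repair this.

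The size of the bias is not derivable from the document. Under the assumed moderate confounding, the spurious slope is 0.02 to 0.06 and the false-positive rate about 8% to 26%. The part compatible with a total ICC of 0.01 reaches about 19%. These figures illustrate the mechanism and are not estimates for this study.

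The conclusion does not extend to practice size, which is a matter for sensitivity analysis. Nor do the documents support calling the survey and claims rules a contradiction.

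**What to change.** State in Phase 4, Step 2 that the main models contain the network characteristic, age, sex and comorbidities, with the random practice effect. Report the models without patient covariates as secondary. Keep the further exploration of patient characteristics for other variables or for effect modification.

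Add a sensitivity analysis that includes practice or network size, and say that size is linked by definition to density and maximum degree, so a change in the coefficient may reflect mechanism as well as confounding.

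The patient questionnaire already covers sociodemographics and diseases, so no new data collection is foreseen. The cost is slight extra analysis work and the loss of some patients with missing covariates, for whom the plan should state a rule.
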